### 6.5.1 Secondary analyses

Secondary analyses will consider the impact of the intervention by comparing mean and the variability of patient wait times and score of satisfaction between the intervention and control sites. We will run similar bivariable comparisons to examine how these factors may be associated with potential confounders. Then, paired t-tests will be used to examine the mean differences between the two groups for the variable of patient wait times and other secondary outcomes. Conditional multivariable analyses will be used to account for matched analyses as well as potential confounders. In addition, we will

describe compliance to the intervention and qualitative assessment on process successes and failures as well as patient and staff satisfaction.

#### 6.5.2 Stopping Rules

Midline analyses will be conducted and the study will cease should there be evidence of a beneficial effect of the intervention of a least a 20 percent difference between the intervention and control sites.

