## 4 AIMS

The primary aim is to determine the impact of clinic efficiency and supply chain quality interventions on the proportion of stable patients on 3-month refills at 4 months post intervention.

The secondary aims are as follows:

- a) Estimate the effectiveness of improved clinic efficiency and supply chain quality on other factors associated with antiretroviral therapy (ART) outcomes at 4 months post intervention such as patient wait times and patient satisfaction
- b) Assess the factors that enable the intervention to be successful, including qualitative process measures
  - Patient satisfaction and perceptions of quality of care
  - Patient experiences with transition to multi-month refills
  - Patient and clinician perceptions on reliability of supply chain
  - Clinician perspectives on barriers or challenges to providing multi-month refills
  - Compliance to quality improvement standard operating procedures

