## 6 RESEARCH PLAN

### 6.1 Study design

We will conduct a cluster randomised, pair-matched, difference in difference study to assess the impact of the intervention on the proportion of 3-month refill scripts. To assure that the two arms (i.e. the control and the intervention arms) are as comparable as possible, facilities will be matched into pairs based on important factors associated with the primary outcome including the proportion of patients on 3-month refills at baseline, the size of the facility, staff-to-patient ratio (active ART patients) and distance from the Medical Stores Limited (MSL). After pair matching, one facility from each pair will be

randomly assigned to undergo the intervention with a 3-month period of assessment and baseline data collection, followed by a 4-month period of the intervention. To assess facility-level outcomes data will be collected in various formats including patient records, patient exit interviews, provider interviews and other relevant key informant interviews.

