## Primary Outcome

The primary outcome is the proportion of stable ART patients receiving 3-month refills, defined as:

The number of stable patients given a 3-month refill in the previous month divided by the total number of stable patients seen in the last month.

Stable patients are defined as:

A patient active in ART care for more than 6 months and on first-line treatment as outlined in the Zambia Consolidated Guidelines (includes the following combinations **(1)** TDF + XTC + EFV, **(2)** TDF + XTC + LPV-r, **(3)** TDF + XTC + ATV-r, **(4)** TDF + XTC + NVP+, **(5)** AZT + 3TC + LPV-r, **(6)** ABC + 3TC + LPV-r, **(7)** ABC + 3TC + EFV).

Secondary outcomes include:

- Patient wait times based on the daily average wait time from entry into the clinic to medication delivery
- Compliance to quality improvement standard operating procedures
- Patient satisfaction and perceptions of quality of care
- Patient experiences with transition to multi-month refills
- Provider perspectives on process of implementing clinical efficiency and supply chain interviews and on barriers or challenges to providing multi-month refills
- Patient and provider perceptions on reliability of supply chain

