#### 6.5.3 Study adaptation

During the midline analyses, we will determine whether any revisions are required to the intervention based on the experience of the first two months.

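### The midline efficacy stop has no defined scale, test or alpha, and obeying it would end the study about two months before its 4-month primary endpoint

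*Combined protocol and SAP*

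**What the plan says.** Section 6.5.2 (Stopping Rules) provides for midline analyses, then states: "the study will cease should there be evidence of a beneficial effect of the intervention of a least a 20 percent difference". The comparison is of intervention with control sites. That is the whole rule.

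Its timing comes from section 6.5.3 (Study adaptation), which uses the same midline to decide "whether any revisions are required to the intervention based on the experience of the first two months".

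The rest of the plan points to a later time. Section 6.1 describes baseline work "followed by a 4-month period of the intervention". The primary aim in section 4 concerns "the proportion of stable patients on 3-month refills at 4 months post intervention", and secondary aim (a) carries the same 4-month time point. The primary analysis in section 6.5 is a matched comparison of change from baseline to endpoint, with stable patients active in care at endline as its denominator. Section 6.4 sets alpha at 0.05 and gives none of it to an interim look.

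**The concern.** A mandatory stop needs a criterion that two analysts would apply in the same way. This one leaves four things open:

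- the scale (percentage points or relative);
- the estimand (difference in levels at midline, or difference in changes from baseline);
- the inferential standard (test or interval, and whether it respects pairing and clustering);
- the consequence for the final alpha.

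Timing adds to the problem. A stop at two months means the 4-month outcome, which the study is designed and powered for, is not observed. The plan does not say whether data collection would continue after a stop, or what would then count as the primary analysis. Stopping because an early estimate is large also selects for overestimates, and section 5.5 and section 6.5.4 show that the estimate is meant to inform scale-up by the Ministry.

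**Working it through.** **1. Timing.** The midline is at about month 2 (6.5.3). A 3-month refill issued on the first intervention day falls due at month 3. The endpoint is at month 4 (sections 4 and 6.1). So no refill issued under the intervention is due by midline. By month 4, those issued in the first month (4 - 3 = 1) have fallen due.

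**2. The plan's own sample size.** Inputs from section 6.4: two-sided alpha 0.05, power 0.80, m = 3845 × 0.8 = 3076, rho = 0.1. The design effect is 1 + 3075 × 0.1 = 308.5, and (1.96 + 0.84)² = 7.85. I read the plus sign before the design effect as multiplication.

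- Text effect of 14 points (15% v 1%, where 15% is my assumption, 1% + 14): c = 2 + 7.85 × (0.1275 + 0.0099) × 308.5 / (3076 × 0.14²) = 7.52. That is 8 per arm, or 16 facilities, as stated.
- Table inputs, 13% v 1%: c = 8.72, which is 9 per arm.
- Text effect with the plus sign as printed: c = 42.2.

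The 14-point effect therefore reproduces the plan's 16 facilities, and I use it below.

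**3. Standard error (SE) of the between-arm difference.** The plan gives none, so I use a range:

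- implied by 14 points at 80% power: 0.14 / 2.80 = 0.050;
- arm levels both near 23% (section 5.3), 8 facilities per arm: √[2 × 0.23 × 0.77 × 308.5 / (3076 × 8)] = 0.067;
- arm levels both at 50%: √[2 × 0.25 × 308.5 / (3076 × 8)] = 0.079.

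Fewer patients at midline would barely change this. The variance factor is rho + (1 - rho)/m, which is 0.1003 at m = 3076 and 0.1006 at half that.

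**4. Behaviour of the rule, normal approximation.** The rule is taken to fire when the estimate reaches the threshold.

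- Chance of stopping: 1 - Φ(z), with z = (threshold - true effect)/SE.
- Mean estimate given a stop: true effect + SE × φ(z)/[1 - Φ(z)].

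Example with SE 0.050 and true effect 0.14: z = 0.06/0.050 = 1.20. The chance is 0.115 and the mean is 0.14 + 0.050 × 0.194/0.115 = 0.224.

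| SE | Stop, no effect (20 points) | Stop, true 14 (20 points) | Mean estimate on stopping, true 14 | Stop, no effect (relative, 4.6 points) |
|---|---|---|---|---|
| 0.050 | 0.003% | 11.5% | 22.4 points | 17.9% |
| 0.067 | 0.13% | 18.4% | 23.6 points | 24.5% |
| 0.079 | 0.58% | 22.4% | 24.6 points | 28.1% |

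The relative threshold is 0.20 × 23% = 4.6 points.

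**5. Sensitivity.** Using the formula's own variance at 15% v 1% with 8 per arm gives SE √[0.1374 × 308.5 / (3076 × 8)] = 0.0415. The rule then fires 7% of the time at a true 14 points, with a mean estimate of 21.9 points. I leave this outside the main range because it treats changes as if they were proportions close to zero.

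**The case against.** The best defence is that the study is a rapid evaluation requested by the Ministry (section 2). On that view, a threshold of 20 points sits well above the 14-point design effect and is conservative. This stands in part. On the absolute scale false stopping is below 1%, and that scale is the natural one: the facility inclusion criterion pairs room for a 20% rise with a ceiling of 80%, and section 6.4 uses % for a difference in changes. But section 6.5.2 does not state the scale. Nor do the documents show what an early stop would gain. Section 6.3.4 limits the study's risks to access to identifiable information, and makes rollout depend on a Ministry decision.

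A reader might infer several stronger points that the documents do not support:

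- **That the rule acts on a bare point estimate.** The text asks for evidence of benefit. The criterion is undefined, and the documents do not show it to be untested.
- **That no midline outcome can be computed.** The Primary Outcome definition, "The number of stable patients given a 3-month refill in the previous month divided by the total number of stable patients seen" over a one-month window, can be evaluated at midline. What is missing then is the 4-month value and the endline denominator of section 6.5.
- **That the midline measure is biased because switched patients are absent.** This depends on how refill lengths persist between visits. If the length is redrawn at each visit, the distortion disappears. The section 6.5 denominator of all active stable patients would not drop absent patients at all.
- **That the midline says nothing about whether stock can sustain longer refills.** Moving patients to 3 months raises the quantity dispensed at once, 23% of patients in the preliminary assessment already received 3-month refills, and Annex 5 records stock-outs by date. Only repeat supply to newly switched patients is unseen, and the 4-month endpoint itself shows that only for first-month switchers.

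**Conclusion.** The concern holds as an undefined mandatory stop, placed before the planned endpoint, that overstates the effect when it fires. If the true effect is 14 points, the overstatement on stopping is about 8 to 11 points (22.4 - 14 to 24.6 - 14).

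These figures rest on 20 absolute points, a normal approximation, SEs that I derived because the plan states none, and a midline effect equal to the 4-month effect. Type I error is not the main problem on the absolute scale. It becomes one on the relative scale, where the false-stop rate is about 18-28%. That the error rate depends so heavily on an unstated scale is itself reason to change the text. The loss of the 4-month outcome needs no such assumptions: it follows from reading section 6.5.2 beside sections 4, 6.1 and 6.5. The plan should be changed before any midline data are compared between arms.

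**What to change.** Delete the efficacy stop from section 6.5.2. Keep the midline only for the operational review in section 6.5.3, and run all 16 facilities to the 4-month endline as the primary analysis.

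If a midline efficacy look is kept, state:

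- the measure, as an absolute difference between arms in change from baseline;
- a pair-level analysis;
- a pre-specified group-sequential boundary with the matching final alpha, allowing for the same 16 facilities contributing to both looks;
- that the 4-month outcome will be collected and reported whatever the midline shows.

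The cost is protocol wording, since endline record extraction is already planned. The downside is that a Ministry decision on scale-up may come about two months later if the effect is large.

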#### 6.5.3 Study adaptation

During the midline analyses, we will determine whether any revisions are required to the intervention based on the experience of the first two months.

#### 6.5.4 Dissemination

The work from this impact evaluation will be shared directly with the MOH and stakeholders to inform the potential scale up of the proposed intervention. Additionally, the results from this work will be shared with community audiences who participated in the work by presenting findings to the facilities and all key stakeholders where appropriate.

## 7 ADMINISTRATIVE ASPECTS

### 7.1 *Monitoring*

Study monitoring will be the responsibility of the Study Coordinator, [name] of the Clinton Health Access Initiative, and will be conducted according to standard operating procedures.

### 7.2 *Recording of data*

Source data will be collected in study workbooks, either in paper format or in electronic form with direct data entry utilising tablets. All data will be entered into a secure electronic database. The Case Report Form (CRF) will be an electronic data file compromised of core data fields. Data will be entered directly into electronic CRFs via a secure web interface. All entries on the CRF must be backed up by source data, unless there is a note to file specifying a deviation from this requirement for a specific purpose.

Workbooks and source data must be kept in order and up-to-date so that they always reflect the latest observations on the participants enrolled in the study. Entries into workbooks must be legible and any changes or corrections to the workbook should not obscure the original entry. Handwritten entries are to be done using a non-soluble/non-smudging ball point pen. Errors are to be corrected by passing a single line through the error and accompanied by the researcher's initials and date. White-out fluid is not to be used under any circumstance. Signature logs of all study staff are to be retained in the Central Investigator files.

### *7.3 Data quality control*

Following completion of each component of the CRF, the data will be checked for consistency, logic and range, either through the process of direct data entry into an eCRF or through analyses of the study database. Queries will be generated for spurious data and clarification sought in writing from the Principle Investigator or delegate. Data query forms will then be forwarded back to the staff responsible for database amendment. If necessary, source documents may need to be accessed to correct data errors.

### *7.4 Confidentiality*

All identifiable information on study subjects will be retained in password protected files and locked cabinets at study sites. Access to this information will only be provided to immediate study staff who have signed confidentiality agreements. No identifying information will be included in study reports.

## ART Register Data Collection Form

### VERIFICATION AND FACILITY INFORMATION

|                                      |             |                  |                          |
|--------------------------------------|-------------|------------------|--------------------------|
| Data is complete and accurate | Name | Signature | Date (dd/mm/yyyy) |
| 2.1 Enumerator                |             |                  | / / 2014                 |
| 2.2 Supervisor                |             |                  | / / 2014                 |
| 2.3 Name of facility          |             |                  |                          |

ELIGIBILITY: ALL PATIENTS ON 1ST LINE TREATMENT, 18YEARS OLD OR OVER WHO MADE AT LEAST ONE APPOINTMENT DURING THE PREVIOUS 3 MONTHS

### PATIENT INFORMATION

| 2.4 Patient's OPD ID number | 2.5 Sex (M/F) | 2.6 ART start date* (dd/mm/yyyy) | 2.7 Date of Birth | 2.9 Date of most recent appointment (dd/mm/yyyy) | 2.10 Date of next appointment (dd/mm/yyyy) | 2.11 Name of digital photograph files | 2.12 Notes or comments |
|-----------------------------|---------------|----------------------------------|-------------------|--------------------------------------------------|--------------------------------------------|---------------------------------------|------------------------|
|                             | M F           |                                  |                   |                                                  |                                            |                                       |                        |
|                             | M F           |                                  |                   |                                                  |                                            |                                       |                        |
|                             | M F           |                                  |                   |                                                  |                                            |                                       |                        |
|                             | M F           |                                  |                   |                                                  |                                            |                                       |                        |
|                             | M F           |                                  |                   |                                                  |                                            |                                       |                        |
|                             | M F           |                                  |                   |                                                  |                                            |                                       |                        |

\*If patient has been lost to care and then re-initiated, the date required is the most recent initiation of ART

FACILITY ID

|  |  |  |  |  |  |  |
|--|--|--|--|--|--|--|
|  |  |  |  |  |  |  |
|--|--|--|--|--|--|--|

|                                      |             |                  |                          |
|--------------------------------------|-------------|------------------|--------------------------|
| Data is complete and accurate | Name | Signature | Date (dd/mm/yyyy) |
| Enumerator                    |             |                  | / / 2014                 |
| Supervisor                    |             |                  | / / 2014                 |
| Name of facility              |             |                  |                          |

| FACILITY INFORMATION |                             |                                                                   |      |
|----------------------|-----------------------------|-------------------------------------------------------------------|------|
| NO.                  | QUESTION                    | RESPONSE CODE                                                     | SKIP |
| FC1                  | HOW MANY REGISTERED NURSES? | Number ..... ____ ____
Refused ..... 97
Don't know ..... 98 |      |
| FC2                  | HOW MANY ENROLLED NURSES?   | Number ..... ____ ____
Refused ..... 97
Don't know ..... 98 |      |
| FC3                  | HOW MANY CLINICAL OFFICERS? | Number ..... ____ ____
Refused ..... 97
Don't know ..... 98 |      |
| FC4                  | HOW MANY DOCTORS?    | Number ..... ____ ____
Refused ..... 97
Don't know ..... 98 |      |
| FC5                  | HOW MANY PHARMACISTS?       | Number ..... ____ ____
Refused ..... 97
Don't know ..... 98 |      |
| FC6                  | HOW MANY CLERKS?            | Number ..... ____ ____
Refused ..... 97
Don't know ..... 98 |      |

|  |  |  |  |  |  |  |
|--|--|--|--|--|--|--|
|  |  |  |  |  |  |  |
|--|--|--|--|--|--|--|

|      |                                                                                                                |                                                                      |  |
|------|----------------------------------------------------------------------------------------------------------------|----------------------------------------------------------------------|--|
| FC7  | HOW MANY DAYS IS THE ART CLINIC OPEN IN ONE WEEK?                                                              | Number ..... ____ ____
Refused ..... 97
Don't know ..... 98    |  |
| FC8  | WHAT IS THE FACILITY POPULATION CATCHMENT?                                                                     | Number ..... ____ ____
Refused ..... 97
Don't know ..... 98    |  |
| FC9  | HOW MANY ACTIVE PATIENTS ATTEND THIS FACILITY?                                                                 | Number ..... ____ ____
Refused ..... 97
Don't know ..... 98    |  |
| FC10 | DO SOME PATIENT GROUPS ATTEND ON SPECIFIC ART CLINIC DAYS?                                                     | No ..... 1
Yes ..... 2
Refused ..... 97
Don't know ..... 98 |  |
| FC11 | ARE SOME ART CLINIC DAYS BUSIER THAN OTHERS?                                                                   | No ..... 1
Yes ..... 2
Refused ..... 97
Don't know ..... 98 |  |
| FC12 | WHAT ARE THE OPERATING HOURS OF THE ART CLINIC?                                                                | Number ..... ____ ____
Refused ..... 97
Don't know ..... 98    |  |
| FC13 | DOES THE CLINIC CONDUCT ANY SPECIAL ACTIVITIES TO RETAIN PATIENTS IN CARE OR TRACE PATIENTS LOST TO FOLLOW-UP? | No ..... 1                                                           |  |
|      |                                                                                                                | Outreach..... 2                                                      |  |
|      |                                                                                                                | SMS reminders ..... 3                                                |  |
|      |                                                                                                                | Other:
Specify.....4                                              |  |

FACILITY ID

|  |  |  |  |  |  |  |
|--|--|--|--|--|--|--|
|  |  |  |  |  |  |  |
|--|--|--|--|--|--|--|

### DAILY PATIENT INFORMATION/CLINIC FLOW

| 1
ID | 2
ARRIVAL TIME OF PATIENT |     | 3
REGISTRATION TIME |     | 4
TIME AT TRIAGE |     | 4
CLINICAL ASSESSMENT TIME |     | 4
ART DISPENSED TIME |     |
|---------|------------------------------|-----|------------------------|-----|---------------------|-----|-------------------------------|-----|-------------------------|-----|
| Line    |                              | HRS |                        | HRS |                     | HRS |                               | HRS |                         | HRS |
| 1       |                              |     |                        |     |                     |     |                               |     |                         |     |
| 2       |                              |     |                        |     |                     |     |                               |     |                         |     |
| 3       |                              |     |                        |     |                     |     |                               |     |                         |     |
| 4       |                              |     |                        |     |                     |     |                               |     |                         |     |
| 5       |                              |     |                        |     |                     |     |                               |     |                         |     |
| 6       |                              |     |                        |     |                     |     |                               |     |                         |     |
| 7       |                              |     |                        |     |                     |     |                               |     |                         |     |
| 8       |                              |     |                        |     |                     |     |                               |     |                         |     |
| 9       |                              |     |                        |     |                     |     |                               |     |                         |     |
| 10      |                              |     |                        |     |                     |     |                               |     |                         |     |

|                                      |             |                  |                          |
|--------------------------------------|-------------|------------------|--------------------------|
| Data is complete and accurate | Name | Signature | Date (dd/mm/yyyy) |
| Enumerator                    |             |                  | / / 2014                 |
| Supervisor                    |             |                  | / / 2014                 |
| Name of facility              |             |                  |                          |

FACILITY ID

|  |  |  |  |  |  |  |
|--|--|--|--|--|--|--|
|  |  |  |  |  |  |  |
|--|--|--|--|--|--|--|

